## **10. DATA HANDLING AND RECORD KEEPING**

### **10.1 Source Data**

Source data will be maintained at site and kept in accordance with GCP. They will be made available for monitoring, audit, and inspection. Study specific information will be primarily recorded on the CRF. These items will be clearly identified in the source data agreement.

### **10.2 CRF and QoL questionnaire Completion**

In all cases it remains the responsibility of the Investigator to ensure that the CRF has been completed correctly and that the data are accurate. This will be evidenced by the signature of the investigator (CI or PI) on the CRF. The completed originals will be stored at the PC-CRTU and a copy filed in the Trial Master File.

QoL questionnaires will be administered and completed by the participant at the clinic visit. QoL questionnaire completion and training will be overseen by a named individual who can answer any questions the participant may have regarding the rationale and method of assessment. The participant will be asked to complete the questionnaire during the clinic visit (prior to other clinical assessments). Ideally the questionnaire should be completed by the participant alone (without assistance from friends, family or the clinical or research team). Any assistance or proxy completion will be recorded and flagged to the trials office. On completion, the QoL questionnaires will be checked on site by a member of the research team for missing data. The participant will be given the opportunity to complete any missing data. If for any reason, the participant is unable to complete the QoL questionnaires during the clinic appointment, the QoL questionnaire can be given to the participant to complete at home. The completed QoL should be completed and sent back to the trials office using a supplied stamped addressed study envelope. Any questionnaires returned in the post will be checked for missing data. Participants will be contacted by telephone and given the opportunity to complete any questions they have missed out. QoL questionnaires must be checked and any missing data completed within 1 week of questionnaire being given to the patient.

Staff delegated to complete CRFs will be trained to adhere to the following CRF completion guidelines:

- Entries on the CRF will be made in ballpoint pen, using blue or black ink.
- Errors will be crossed out with a single stroke and the correction will be inserted and the change initialled and dated. If it is not clear why a change has been made, an explanation should be written next to the change. Correction fluid should not be used.
- QoL questionnaires to be completed in accordance with completion instructions.
- Participants will be encouraged to answer all questions when completing the CRFs and the QoL questionnaires.
- QoL questionnaires will be checked for missing data and where feasible participants will be given the opportunity to complete any missing data.
- Data reported on each CRF should be consistent with the source data or the discrepancies should be explained.
- Reasons for missing data should be documented on the CRF / questionnaire.
- Where information is not known or refused, this will be clearly indicated on the form

### **10.3 Data Management**

The IMPRESS-AF database system will be located within PC-CRTU.

The security of the System is governed by the policies of the University of Birmingham. The University's Data Protection Policy and the Conditions of Use of Computing and Network Facilities set out the security arrangements under which sensitive data should be processed and stored. All studies

---

|                          |            |               |            |       |          |
|--------------------------|------------|---------------|------------|-------|----------|
| Trial name:              | IMPRESS-AF |               |            |       |          |
| Protocol version number: | 6.0        | version date: | 12/10/2015 | Page: | 39 of 67 |

at the University of Birmingham have to be registered with the Data Protection officer and data held in accordance with the data protection act. The University will designate a Data Protection Officer upon registration of the study. The Study Centre has arrangements in place for the secure storage and processing of the study data which comply with the University of Birmingham policies.

The System shall incorporate the following security countermeasures:

- Physical security measures: including restricted access to the building, supervised onsite repairs and storages of back-up tapes/disks are stored in a fire-proof safe.
- Logical measures for access control and privilege management: including restricted accessibility, access controlled servers, separate storage of non-identifiable data etc.
- Network security measures: including site firewalls, antivirus software, separate secure network protected hosting etc.
- System Management: the System shall be developed by the PC-CRTU Programming Team and will be implemented and maintained by the PC-CRTU Programming Team.
- System Design: the system shall comprise of a database and a data entry application with firewalls, restricted access, encryption and role based security controls.
- Operational Processes: the data will be processed and stored within the Study Centre (University of Birmingham).
- Data processing: Statisticians will only have access to anonymised data.
- System Audit: The System shall benefit from the following internal/external audit arrangements:
  - Internal audit of the system
  - An annual IT risk assessment
- Data Protection Registration: The University of Birmingham has Data Protection Registration to cover the purposes of analysis and for the classes of data requested. The University's Data Protection Registration number is Z6195856.

Storage of personal data on manual files; paper - copies of questionnaires, paper copies of results, spreadsheets, lab reports, consent forms and CRFs will be held in secure data storage such as lockable filing cabinets in a restricted access environment. Storage of data on university computer and NHS desktop computers; will be kept in password protected, access limited electronic format. The clinical trial information including CRF will be entered onto an online database and will be anonymised at point of entry. Data entered will be stored on secure servers held at the University of Birmingham.

Manual files containing personal information and allocated identifiers will be kept in a separate location at the RC-CSS to the anonymised data. All computer data that are patient identifiable, will be stored separately from the non-identifiable data when they are no longer required for linking or quality checking. All data will be strictly handled in accordance with the Data Protection Act and NHS Code of Confidentiality. All data analyses will be done on fully anonymised data.

## 10.4 Archiving

To enable monitoring, peer review and audits from Health Authorities, the Investigator must agree to keep records; including the identity of all participating subjects (sufficient information to link records e.g. CRFs, blood results and GP notes), all original signed Informed Consent Forms, signed original blood data, copies of all CRFs and detailed records of drug destruction.

It is the responsibility of the Site Principal Investigator(s) to ensure all essential trial documentation and source documents (e.g. signed Informed Consent Forms, Investigator Site Files, Pharmacy Files, participants' hospital notes, copies of CRFs etc.) at their site are securely retained for 20 years. The PC-CRTU trials team will be responsible for arranging the archiving of the TMF. No documents will be destroyed without prior approval from the Sponsor.

|                          |            |               |            |       |          |
|--------------------------|------------|---------------|------------|-------|----------|
| Trial name:              | IMPRESS-AF |               |            |       |          |
| Protocol version number: | 6.0        | version date: | 12/10/2015 | Page: | 40 of 67 |

## **11. QUALITY CONTROL AND QUALITY ASSURANCE**

### **11.1 Site Set-up and Initiation**

All participating Investigators will be asked to supply a current CV to PC-CRTU. All members of the site research team will also be required to sign the Site Signature and Delegation Log. Prior to commencing recruitment all sites will undergo a process of site initiation. Key members of the site research team will be required to attend either a meeting or a teleconference covering aspects of the trial design, protocol procedures, Adverse Event reporting, collection and reporting of data and record keeping. Sites will be provided with an Investigator Site File and a Pharmacy File containing essential documentation, instructions, and other documentation required for the conduct of the trial. The PC-CRTU trials team must be informed immediately of any change in the site research team.

### **11.2 Monitoring**

#### **11.2.1 Onsite Monitoring**

Monitoring will be carried out as required following a risk assessment and as documented in the monitoring plan. Any monitoring activities will be reported to the trials team and any issues noted will be followed up to resolution. Additional on-site monitoring visits may be triggered, for example by poor CRF return, poor data quality, low SAE reporting rates, excessive number of participant withdrawals or deviations. If a monitoring visit is required the Trials team will contact the site to arrange a date for the proposed visit and will provide the site with written confirmation. Investigators will allow the IMPRESS-AF monitor to access to source documents as requested. The monitoring will be conducted by PC-CRTU.

Investigators will allow the trial monitors access to source documents as requested. If a monitoring visit is required the PC-CRTU will contact the site to arrange a date for the proposed visit. Data to be verified will include:

- Informed Consent
- Eligibility
- Adverse Events

Any serious breach highlighted will be forwarded to the Trial Manager and the Sponsor as soon as possible. The sponsor will then notify the licensing authority in writing of any serious breaches of:

- The conditions and principles of GCP
- The protocol

The Sponsor must notify the licensing authority within 7 days of becoming aware of the breach.

#### **11.2.2 Central Monitoring**

Trials staff will be in regular contact with the site research team to check on progress and address any queries that they may have (by phone/fax/ email/letter). Trials staff will check incoming Case Report Forms for compliance with the protocol, data consistency, missing data and timing.

Monitoring will be done according to the PC-CRTU Monitoring SOP and the Monitoring Plan.

The Trial Coordinator will be in regular contact with the site personnel (by phone/fax/ email/letter) to check on progress and answer any queries that they may have. Trial staff will check incoming CRFs for compliance with the protocol, consistent data, missing data, timing and Investigator sign-off.

|                          |            |               |            |       |          |
|--------------------------|------------|---------------|------------|-------|----------|
| Trial name:              | IMPRESS-AF |               |            |       |          |
| Protocol version number: | 6.0        | version date: | 12/10/2015 | Page: | 41 of 67 |

---

### 11.3 Audit and Inspection

The Investigator will permit trial-related monitoring, audits, ethical review, and regulatory inspection(s) at their site, providing direct access to source data/documents. The investigator will comply with these visits and any required follow up. Sites are also requested to notify PC-CRTU of any MHRA inspections.

### 11.4 Notification of Serious Breaches

In accordance with Regulation 29A of the Medicines for Human Use (Clinical Trials) Regulations 2004 and its amendments the Sponsor will notify the licensing authority in writing of any serious breach of:

- The conditions and principles of GCP in connection with that trial or;
- The protocol relating to that trial (within 7 days of becoming aware of that breach)
- For the purposes of this regulation, a "serious breach" is a breach which is likely to effect to a significant degree:
- The safety or physical or mental integrity of the subjects of the trial; or
- The scientific value of the trial

Sites are therefore requested to notify PC-CRTU who will be responsible for notifying the RGT and CRCT UoB of any suspected trial-related serious breach of GCP and/or the trial protocol. Where PC-CRTU is investigating whether or not a serious breach has occurred sites are also requested to cooperate with PC-CRTU in providing sufficient information to report the breach to the MHRA where required and in undertaking any corrective and/or preventive action.

---

|                          |            |               |            |       |          |
|--------------------------|------------|---------------|------------|-------|----------|
| Trial name:              | IMPRESS-AF |               |            |       |          |
| Protocol version number: | 6.0        | version date: | 12/10/2015 | Page: | 42 of 67 |

[figure not shown]

|                          |            |               |            |       |          |
|--------------------------|------------|---------------|------------|-------|----------|
| Trial name:              | IMPRESS-AF |               |            |       |          |
| Protocol version number: | 6.0        | version date: | 12/10/2015 | Page: | 43 of 67 |

**12. END OF TRIAL DEFINITION**

The end of trial will be the last visit of the last patient. Sufficient time will be allowed for the completion of protocol procedures, data collection and data input. The PC-CRTU trial team will notify the MHRA, main REC and RGT that the trial has ended within 90 days of the end of trial and will provide them with a summary of the clinical trial report within 12 months of the end of trial.

---

|                          |            |               |            |       |          |
|--------------------------|------------|---------------|------------|-------|----------|
| Trial name:              | IMPRESS-AF |               |            |       |          |
| Protocol version number: | 6.0        | version date: | 12/10/2015 | Page: | 44 of 67 |

## 13. STATISTICAL CONSIDERATIONS

### 13.1 Analysis of Outcome Measures

Analysis will follow intention to treat principles (ITT) Following data cleaning, levels of demographics gathered at primary screening will be quantified using basic statistics (mean, SD, Median, IQR) and graphical presentations (boxplots, histograms, scatter plots) Sub division will be made by intervention /control and stratum. Likewise levels of primary and secondary outcomes at baseline will be similarly reported. Prior to any substantial analysis, preliminary impression of trends in longitudinal measurements will be provided graphically, separately for intervention and control participants.

1. Linear mixed model analysis will be used to compare peak  $VO_2$  at two years between the intervention and the control group Covariates will be baseline peak  $VO_2$ , age, gender systolic/diastolic blood pressure and BMI measured at baseline. GP practices or recruitment centres will be included as random effects to enable findings from this trial to be judged in the context of a different group of GP practices

2. Further exploratory analyses will incorporate interaction terms between intervention/control and each of the covariates. Backward elimination will be used to remove non significant interactions and then non significant main effects. If residuals from mixed model analysis violate the assumption of a normal distribution as tested by Kolmogorov Smirnov test then transformation of the dependent variable or bootstrap analysis will be conducted. Transformations considered will be those in the Box Cox family i.e. power and log. Bootstrap analysis will involve sampling with replacement 1000 sets of data from the original data, each of the same size as the original dataset Each set will then be analysed in the same manner as the original dataset This will enable an empirical distribution of each test statistic to be formed and relocated at its null hypothesis value Significance of the statistics in the original data will then be determined from the appropriate tail area of the empirical null distribution.

Secondary analyses will also use linear or non linear mixed modelling as above but with dependent variable the secondary end points mentioned in the earlier Trial End Points section Interactions between intervention/control, and age and gender will also be included in the mixed modelling analyses to see whether differences in secondary endpoints between intervention and control participants vary with these two factors. Each mixed model analysis will be run additionally separately on each stratum. The primary QoL analysis will be the change in the overall QoL score between treatment groups over the two year duration. This will include baseline measures as a covariate. Full analysis will therefore be completed at the 24 months period and this will form the principle QoL analysis. The 12 month QoL assessments will allow a preliminary analysis to be undertaken to determine if changes occur within the first 12 months. These repeated measures will allow further exploratory analysis of changes in QoL to be undertaken to explore which domains are driving the changes in the QoL scores.

3. Missing values will be substituted using a multiple imputation procedure. Because of the likelihood of non normality the method of Hussain will be used. This replaces the data by its Normal scores, imputes using these transformed data and then uses a polynomial relationship between Normal scores and untransformed data to give a complete set of data. This is then repeated 10 times and variation seen between repetitions and within are used to estimate the uncertainty in the imputed mean value.

In the case of missing data due to death of the participant during the trial a comparative analysis will be conducted between surviving participants and the deceased. If no difference is apparent then MI will be performed on all of the data but otherwise a complete case analysis will be conducted and a report compiled setting out the difference between the deceased and the surviving participants.

|                          |            |               |            |       |          |
|--------------------------|------------|---------------|------------|-------|----------|
| Trial name:              | IMPRESS-AF |               |            |       |          |
| Protocol version number: | 6.0        | version date: | 12/10/2015 | Page: | 45 of 67 |

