### 13.1.1 Power Calculations

We will send invitations to 1280 potential participants from 64 GP practices with the aim of recruiting 640 for further testing. 250 of the screened participants will then be randomised. In addition, suitable participants from outpatient clinics run by [name] and [name] will also be invited to take part.

Our primary outcome will be based on a 'gold' standard test of exercise tolerance defined by peak  $\text{VO}_2$  using CPET and assessed at baseline and after the treatment with the trial drug. We hypothesise that the spironolactone will improve peak  $\text{VO}_2$  compared to the placebo treated subjects. We base our power calculation for peak  $\text{VO}_2$  on the published values of peak  $\text{VO}_2$  in subjects with HFpEF ( $16 \pm 5$  ml/min/kg). We anticipate a difference of 2ml/min/kg in the improvement in peak  $\text{VO}_2$  after 2-year treatment with spironolactone compared with the control group. Unfortunately this publication does not give a standard deviation on the change in peak  $\text{VO}_2$  from baseline but a similar trial, Edelmann et al provides that statistic (5 ml/min/kg) and also reports a similar magnitude of effect.

A sample size of 100 patients in each group will have 80% power to detect a difference in means of 2.000 assuming that the common standard deviation is 5.000 (effect size =0.40) using a two group t-test with a 0.05 two-sided significance level. Sample size calculation was conducted using the nQuery software. Approximately, for 80% power at 5% significance, sample size in each group would be  $15.68/(\text{effect size})^2$ . To accommodate a loss to follow-up of 20% of patients from each group would imply initially recruiting a total sample size of 250 ( $250 \times 0.8 = 200$ ) in order to still retain 200 patients in all. Loss of 20% of patients would still enable effects in excess of 2.3ml/min/kg (effect size=0.46) to be detected with 90% power at the 5% significance level. Sample size= $21.0/(\text{effect size})^2$  for 90% power, 5% significance. At the other extreme zero loss to follow up from 250 patients would lead to 88% power to detect a 2 ml/min/kg at 5% significance Prediction of 20% loss to follow up is based on a 10% loss per year and composed of 5% due to death and 5% due to other reasons. The relevant population of patients would be under regular follow up and as such would have relatively lower expected mortality.

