**Sample size – calculations:** The sample size has been originally calculated to provide sufficient power to assess impact of the spironolactone treatment for the outcomes of the IMPRESS-AF trial and it will provide statistical power sufficient to assess utility of the fibrotic parameters to predict the study outcomes and efficacy of treatment with spironolactone (with more 80% power) using appropriate regression analysis (linear regression and Cox regression). Further exploratory analyses will incorporate interaction terms between intervention/control and each of the covariates, including parameters of fibrosis. Backward elimination will be used to remove non-significant interactions and then non-significant main effects.

Regarding the nitrite/platelet part of the study we aim to obtain pilot data for a future bigger and specifically designed study. Based on our previous studies it is estimated that n=20 AF patients will be necessary for the evaluation of plasma nitrite concentrations. For platelet aggregation studies, previous studies utilised n=14 HF patients for the determination of the effect of GTN in whole blood. Based on the above, we estimate that n=40 HF patients will be sufficient to determine the effects of nitrite on aggregation and at molecular level in isolated platelets in comparison to healthy controls (n=20 for platelet aggregation, n=20 for western blot).

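### The exploratory interaction models use backward elimination that does not exempt randomised treatment or parent main effects, so only the survivors of an undisclosed search are reported

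*Protocol*

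**What the plan says.** Section 13.1 of the Protocol sets out the analysis in numbered items.

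- **Item 1, primary analysis.** "Linear mixed model analysis will be used to compare peak" VO2 at two years between the arms. The covariates are baseline peak VO2 plus "age, gender systolic/diastolic blood pressure and BMI measured at baseline", with practice or recruitment centre as a random effect. Item 1 has no selection step.
- **Item 2, exploratory analysis.** "Further exploratory analyses will incorporate interaction terms between intervention/control and each of the covariates". The next sentence is the rule at issue: "Backward elimination will be used to remove non significant interactions and then non significant main effects".
- **Secondary endpoints, same section.** These use mixed models described by reference back to the preceding modelling, with treatment interactions for age and gender. The text does not say whether the elimination step comes with that reference.
- **Appendix 1, sample size paragraph.** After linear and Cox regression are named for the biomarker aims, further exploratory models add treatment interactions with the covariates, now including fibrosis parameters. The same rule follows: "Backward elimination will be used to remove non-significant interactions and then non-significant main effects".

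**The concern.** The rule as written has three consequences for the exploratory models.

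1. **Treatment can be dropped.** It is one of the main effects that the second stage may remove. The exploratory model then shows no treatment estimate and no interval.
2. **A parent main effect can be dropped while its interaction stays.** If the treatment main effect goes and a treatment-by-age term remains, the fitted model forces a zero treatment effect where the age variable equals zero. The result then depends on how age was coded or centred.
3. **Only survivors are shown.** Their p-values and intervals are computed as if the final model had been chosen in advance. The reader does not see the interactions that were tried and removed.

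At stake is what the trial says about who benefits. This matters most in Appendix 1, where using biomarkers to predict the efficacy of spironolactone is a stated aim (aim ii) and a stated hypothesis. The interactions that bear on that aim are named only in the sentence just before the elimination rule.

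**Working it through.** **Plan's own figures.** Section 13.1.1 states: "A sample size of 100 patients in each group will have 80% power to detect a difference in means of 2.000", with SD 5 and "using a two group t-test with a 0.05 two-sided significance level". Effect size = 2/5 = 0.40, and the plan's approximation gives 15.68/0.40² = 98 per arm. Computed power at 100 per arm is 80.4% by t-test. With 250 × 0.8 = 200 analysed, the dropout allowance is consistent. At 125 per arm, power is 88.3% against the stated 88%. These figures reproduce. The protocol gives no error rate for the elimination procedure.

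**Number of interactions.** Baseline peak VO2, age, gender, systolic BP, diastolic BP and BMI give six. If blood pressure enters as one term, there are five.

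**Chance of keeping at least one false interaction.** The retention threshold is not stated, so 5% is assumed. For k independent tests with no true effect modification the chance is 1 − (1 − α)^k:

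- k = 5: 1 − 0.95⁵ = 22.6%
- k = 6: 1 − 0.95⁶ = 26.5%

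| Assumed threshold | k = 5 | k = 6 |
|---|---|---|
| 0.01 | 4.9% | 5.9% |
| 0.05 | 22.6% | 26.5% |
| 0.10 | 41% | 47% |
| 0.157 | 57% | 64% |

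**Simulation check.** Settings: 4,000 trials each, ordinary least squares without the practice effect, residual SD 5, no true interactions, systolic-diastolic correlation 0.6 (assumed) and elimination at 5%. At least one interaction was kept in 23.2% of trials with five interactions and in 26% to 28% with six, in line with the formula.

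**How often treatment is removed from the exploratory model.** The simulation counts trials in which all six interactions were eliminated and treatment was then dropped. It can be compared with a simple product: the chance that treatment is non-significant, times 1 − 0.265 = 0.735 for no interaction kept. At SD 5 and 100 per arm, SE = 5 × √(2/100) = 0.707.

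| True effect (ml/min/kg), n | Non-significant | × 0.735 | Simulated |
|---|---|---|---|
| 0, n = 200 | 0.950 | 70% | 68% |
| 1, n = 200 | 0.707 | 52% | 53% |
| 2, n = 200 | 0.193 | 14% | 15% |
| 2, n = 250 | 0.115 | 8.4% | 8.5% |

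The product nearly reproduces the simulation, so these removal rates are essentially ordinary non-significance. They depend on the residual SD. If the covariates explained a quarter of the variance (assumed), the SD would be 5 × √0.75 = 4.33 and the SE 0.612. The figure for a true effect of 2 at n = 200 would then be about 0.10 × 0.735 = 7%.

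**Appendix 1, illustration only.** Adding the three fibrosis markers named in its methods (PICP, PIIICP, galectin-3) to five or six covariates gives eight or nine interactions: 1 − 0.95⁸ = 34% and 1 − 0.95⁹ = 37% per outcome, assuming independent tests at 5%.

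**The case against.** The strongest reply is that elimination is confined to analyses that the protocol itself calls exploratory. Item 1 keeps treatment and a fixed covariate list, and reports the treatment effect whatever item 2 does. This stands. A reader might infer from the rule that the primary treatment effect could disappear from the results; the document does not support that.

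A reader might also take the removal rates, 68% under no effect for example, as damage done by elimination. They are not. A fixed model would find treatment non-significant at least as often. What elimination adds is that the estimate and interval vanish from that model instead of being shown.

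Third, a rate of about a quarter is what five or six unadjusted exploratory tests give. Testing interactions one at a time gives about the same chance that some interval excludes zero. This also stands, so the rate measures the size of the search and does not argue for one method over another.

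Fourth, thresholds, hierarchy rules and forced-in terms for exploratory models are commonly left to an SAP, which is not at hand. That covers the missing threshold. It does not cover the rule itself: the protocol states the procedure and its order, and an SAP that followed it would inherit the problem.

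Finally, Appendix 1 names linear and Cox regression for its aims before it turns to the exploratory models, and the simulation did not model biomarkers. The appendix is therefore affected by the same wording, but no measured size attaches to it.

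**Conclusion.** The point holds as a low-severity, inexpensive correction to the exploratory interaction models in section 13.1 item 2 and Appendix 1. The stated rule lets treatment or a parent main effect be removed, and reports only survivors with inference that ignores the selection. The chance of presenting at least one false effect modifier is about 23% (five interactions) to 26% (six). This rests on a 5% retention threshold that the protocol does not state, near-independent tests and no true effect modification.

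The primary treatment estimate is unaffected. Whether the secondary-endpoint models are affected cannot be settled from the text, because the reference back to the earlier modelling could be read either way.

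**What to change.** - **Section 13.1 item 2 and Appendix 1:** delete the backward elimination sentence. Replacement wording could be:

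> All exploratory models will retain randomised treatment and every listed covariate. Each treatment-by-covariate interaction will be added singly to this model. All interaction estimates will be reported with 95% confidence intervals, whatever their significance, together with the number examined, and will be labelled exploratory.

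- **Section 13.1, secondary endpoints:** state that the reference back to the earlier modelling does not bring elimination into these models.

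The change does not reduce the familywise false-positive rate. It shows how many interactions were examined and gives intervals that do not depend on which terms survived. The cost is slightly longer reporting and a less compact model; data collection, sample size and the primary analysis do not change.

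### The residual-normality rule in Section 13.1 item 2, if it reaches the primary model, can move the peak VO2 effect off the ml/min/kg scale on which the trial is planned

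*Protocol*

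**What the plan says.** Protocol Section 13.1, item 1, sets the main comparison of the arms on two-year peak VO2 in the words "Linear mixed model analysis will be used to compare peak" (the quote stops before the VO2 symbol). The model adjusts for baseline peak VO2 and other covariates, with practice or recruitment centre as a random effect. No normality condition is attached there.

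Item 2 begins "Further exploratory analyses will incorporate interaction terms between intervention/control and each of the covariates", goes on to backward elimination, and then gives a rule for the case in which mixed-model residuals are found non-normal: "as tested by Kolmogorov Smirnov test then transformation of the dependent variable or bootstrap analysis will be conducted". On the first branch, "Transformations considered will be those in the Box Cox family i.e. power and log". On the second, 1000 resampled datasets are each analysed like the original, the test statistics are recentred at the null value, and significance is read from the tail area.

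Section 13.1.1 plans the trial in raw units. Its target for peak VO2 reads "We anticipate a difference of 2ml/min/kg in the improvement in peak", the sample size is computed "assuming that the common standard deviation is 5.000 (effect size =0.40"), and a table shows the expected 95% interval as 0.61 to 3.39.

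**The concern.** Item 2 speaks of residuals from mixed model analysis without limiting this to the exploratory models. Mixed model analysis is what item 1 calls the primary analysis, and no other normality rule covers that model. On the natural reading, a significance test on the residuals can therefore change how the primary endpoint is analysed.

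Two things follow.

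- **Scale.** A log or power outcome does not estimate the mean difference in ml/min/kg in which the hypothesis, SD, sample size and expected interval are written.
- **Open choice.** Once the test rejects, the text gives no rule for choosing between transformation and bootstrap, or for choosing the power. That choice would be made after residuals from a model containing treatment have been seen.

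At stake is whether the primary result can be read against the difference that the trial was built to detect.

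**Working it through.** **1. Planned figures and their scale (Section 13.1.1).** Difference 2 ml/min/kg, SD 5, two-sided 5%, 80% power.
- Effect size = 2/5 = 0.40. The protocol's approximation gives 15.68/0.40² = 98 per arm; the t-based calculation gives 99.08, so 100. Power at 100 per arm is 0.804.
- Allowing for 20% loss: 200/0.8 = 250.
- Expected interval: SE = 5 × √(2/100) = 0.71; 2 ± 1.96 × 0.707 = 0.61 to 3.39.

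The figures reproduce, and all are in ml/min/kg.

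**2. What each branch reports.**

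| Branch | Scale of effect | Interval described? |
|---|---|---|
| Item 1 model, untransformed | ml/min/kg | the model supplies one |
| Box-Cox (power or log) | transformed | none; no back-transformation given |
| Bootstrap | ml/min/kg | no, significance only |

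Only the transformation branch changes the scale.

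**3. How often the test might fire.** The protocol gives no residual distribution, so every shape here is an assumption. The matched shapes use the 16 ± 5 of Section 13.1.1 (CV = 5/16 = 31%). Simulation: 200 values, 4,000 runs, plain Kolmogorov-Smirnov test at 5% with estimated mean and SD.

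| Assumed shape | Test rejects |
|---|---|
| Normal | 0% |
| Gamma, matched to 16 ± 5 | about 5% |
| Log-normal, matched to 16 ± 5 | about 25% |
| Gamma, shape 4 (skew 1) | 38% |
| Log-normal, sigma 0.5 | 89% |

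The 0% under normality, against a nominal 5%, shows that the plain test is not at its nominal level when mean and SD are estimated. Whether a correction is intended is not stated, and it matters. For residuals of skew 1 from a baseline-adjusted model, the plain test rejected in 34% of 1,000 runs and the Lilliefors-corrected test in 95%.

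**4. Is the switch needed for validity?** In the shapes of step 3, a two-sample test with 100 per arm kept type I error at about 5%. A baseline-adjusted linear model with 100 per arm and residual SD 5 (4,000 runs; baseline slope 0.75 assumed) gave:

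| Residuals | Type I error | Coverage under the null | Power for 2 ml/min/kg |
|---|---|---|---|
| Normal | 0.048 | 0.952 | 0.79 |
| Skew 1 | 0.050 | 0.950 | 0.80 |
| Skew 1.5 | 0.045 | 0.955 | 0.80 |
| Skew 2 | 0.047 | 0.953 | 0.80 |
| t, 5 df | 0.046 | 0.954 | 0.81 |

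**5. Does the switch itself distort the error rate?** Null simulation, 1,500 runs, skew-1 residuals, Lilliefors-corrected trigger (fired in 94% of runs):
- Box-Cox fixed as the branch: 0.050.
- Bootstrap fixed as the branch: 0.049.
- Most favourable of log, Box-Cox and bootstrap reported: 0.065.

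**The case against.** The strongest reply is about scope. The rule stands in an item that opens as exploratory, directly after interaction terms and backward elimination, while item 1 carries no gate. A reader may fairly hold that it was never meant for the primary model. This stands in part: the scope is not cleanly stated. But the rule's wording is general, and either reading requires the text to be clarified.

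Second, test level, Box-Cox power and back-transformation are details that a SAP may settle, and the SAP was not available for this review. That is fair for the details. It does not answer a rule, already written into the protocol, that allows the primary effect measure to change.

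Third, type I error is not the only criterion. If effects are multiplicative (means 16 and 18, 100 per arm), a log analysis had power 0.77 against 0.75 untransformed at a CV of 31%, and 0.38 against 0.35 for log-normal sigma 0.5. These gains are small but real, so it would be wrong to infer that the switch protects nothing. Outliers, unequal variances and the smaller per-stratum analyses were not tested either.

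Fourth, 2 ml/min/kg is a planning difference, and no success rule compares the estimate with it. That is true; the loss is of interpretability, not of a formal decision criterion.

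**Conclusion.** The point holds as one of estimand and interpretation. On the natural reading of item 2, a data-driven test and an unfixed choice of branch can take the primary effect off the ml/min/kg scale, and validity at about 100 per arm did not need it in any case simulated.

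A reader might infer three stronger things that the documents do not support:

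- **That the primary p-value is invalid.** With one branch fixed in advance, type I error stayed at 0.049 to 0.050. The rise to about 0.065 needs selection on results, in one assumed skew-1 scenario.
- **That the test will usually fire.** Rates of 38% and 89% need more skew than gamma or log-normal shapes matched to 16 ± 5, which give about 5% and 25% with the plain test. A corrected test would fire more often.
- **That the test picks Box-Cox or bootstrap, or that both leave the scale.** It only triggers a departure from the plain model, and the bootstrap stays in ml/min/kg.

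The simulations rest on assumed residual shapes and on models without practice or centre random effects, because the protocol gives neither a residual distribution nor a between-practice variance.

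**What to change.** In Section 13.1:

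- State that the primary analysis is the untransformed mixed model of item 1 whatever any residual test shows, reported as the adjusted mean difference in ml/min/kg with its 95% CI.
- Remove the Kolmogorov-Smirnov gate and the Box-Cox option for the primary endpoint. They may remain for the exploratory models, provided that the text says they apply only there.
- Pre-specify one bootstrap 95% CI on the same scale, resampled within arm and stratum, as a sensitivity analysis.

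The cost is a wording change and one routine extra analysis, with a possible small loss of power if the treatment effect is multiplicative (two to three percentage points in the cases above).
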